**Results:**

Any deviation of the serum TSH by more than 20% from the initial values, while keeping triiodothyronine (T_3_), and thyroxine (T_4_) levels within the normal range, will be deemed statistically significant. Consequently, we anticipate a statistically significant variation in serum TSH levels between the therapeutic enema and Kanchanar Guggul treatments. Presently, the drug preparation operations are in progress. We expect to start enrolling patients in June 2024, do data analysis in December 2025, and acquire results by early 2026, marking the end of this trial.

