### Diagnostic Criteria

The diagnosis of SCH will be made per the *ICD-10* (*International Statistical Classification of Diseases, Tenth Revision*) criteria (SCH) as follows: TSH>4.50 µIU/mL, fT4=0.8-1.8 ng/dL, fT3=1.4-4.4 Pg/mL [13] (Textbox 1).

Eligibility, exclusion, withdrawal, and adverse drug reaction criteria.

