### Screening Investigations

Serum TSH will be measured before and after the study. On the 181st day, serum TSH, T_3_, and T_4_ will be measured. The above findings will be compared to the baseline findings.

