### Criteria of the Assessment or Outcome Variable

A variation of more than 20% of the baseline value of serum TSH with normal values of T_3_ and T_4_ will be considered to determine the efficacy of the intervention. Therefore, decreasing serum TSH with no change in T_3_ and T_4_ means, Kshar Basti with Kanchanar Guggul is efficacious in SCH.

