### Evaluation Outcomes

The primary assessment result of our study is the disparity in the TSH, T3, and T4 levels compared to the initial values. We will deem any deviation of 20% or more from the baseline as statistically significant.

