## Discussion

### Principal Findings

The 45 participants in the control group will receive oral L-thyroxine. On the other hand, the trial group, also consisting of 45 participants, will get a treatment involving Kshar Basti and oral Kanchnar Guggul tablets. Both groups will undergo treatment for 180 days, and on day 181, we will assess the levels of TSH, T3, and T4 in the blood. We will compare the changes before and after therapy. We expect that the Ayurvedic intervention, specifically the combination of Kshar Basti and Kanchnar Guggul, will demonstrate statistically significant outcomes compared to the standard treatment. This would establish Ayurvedic intervention as a viable treatment option for SCH, eliminating the need for lifelong consumption of L-thyroxine tablets by the patient.

Hashimoto thyroiditis typically correlates with hypothyroidism. The thyroid gland produces numerous growth and vasoactive substances. The epithelial cells of the thyroid gland contain the glycoprotein known as vascular endothelial growth factor. It plays a critical role in the elevated levels of TSH in SCH.

A study compared the administration of Nigella sativa powder at a dosage of 2 grams per day for 8 weeks with the administration of placebos consisting of starches at the same dosage and duration. This RCT involved 47 human participants diagnosed with Hashimoto thyroiditis. Nigella sativa treated 23 of them, while starches served as a placebo for the remaining 24. The study determined that Nigella sativa seeds were useful in alleviating Hashimoto thyroiditis. It also successfully reduced vascular endothelial growth factor levels and body weight.

In Ayurveda, Nigella sativa is referred to as “Krishnajeeraka.” In our study, we will be administering Shivakshar Pachak Churna as “Deepan-Pachan” for the first 3 days. Nigella sativa is a constituent of Shivakshar Pachak Churna [16].

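### The stated efficacy rule rests on a before-after fall in TSH in the Ayurvedic arm, which conflicts with the randomised comparison and which regression to the mean can produce

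*Protocol article*

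**What the plan says.** All references are to the protocol article.

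- **Criteria of the Assessment or Outcome Variable.** The yardstick is each participant's own starting value: "A variation of more than 20% of the baseline value of serum TSH with normal values of T_3_ and T_4_ will be considered" to determine efficacy. The conclusion follows directly: "decreasing serum TSH with no change in T_3_ and T_4_ means, Kshar Basti with Kanchanar Guggul is efficacious in SCH".
- **Screening Investigations.** "Serum TSH will be measured before and after the study", with TSH, T3 and T4 on day 181. Then: "The above findings will be compared to the baseline findings".
- **Evaluation Outcomes.** The primary result is again set against initial values: "We will deem any deviation of 20% or more from the baseline as statistically significant".
- **Hypothesis.** It is stated for the Ayurvedic arm only.
- **Methods (Overview), Study Setting, Principal Findings.** These give the opposite picture: an aim to compare with L-thyroxine, a 1:1 randomised superiority design, and an expected significant result against standard treatment.
- **Abstract, Results.** A third contrast is named: "variation in serum TSH levels between the therapeutic enema and Kanchanar Guggul treatments". These are two components of the same arm.
- **Diagnostic Criteria.** Entry requires TSH above 4.50 µIU/mL, with free T4 and free T3 in range.
- **Statistical Analysis.** A Student t test (or z-test) at P below .05, without saying whether it is paired or between arms.
- **Principal Findings.** A positive result is said to lead to "eliminating the need for lifelong consumption of L-thyroxine tablets by the patient".

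**The concern.** A randomised control arm is there to remove whatever would have happened anyway. A rule that reads efficacy from one arm's change since baseline gives up that protection. It matters here because participants are selected for a high value of the variable that is then used as the outcome. Some of those above 4.50 on one sample are there partly through within-person variation, and their next value tends to be lower.

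Two wrong conclusions become possible: an inert regimen is called efficacious, or a regimen that lowers TSH less than L-thyroxine is called efficacious. The second needs no distributional assumption. The condition on T3 and T4 gives little protection, because participants with subclinical disease enter with both in range and an inert regimen would mostly leave them there.

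The remark about lifelong L-thyroxine goes further still. The stated outcome is read on day 181, the day after 180 days of treatment, and says nothing about what happens once treatment has stopped.

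**Working it through.** **1. Plan's own figures.** The article gives no error rate for its efficacy rule, so there is none to reproduce. The per-group size used below is its own: 40 + 5 = 45. The sample size formula is not shown and no SD, effect or power is given, so the 40 itself cannot be rebuilt. Nothing here depends on it.

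**2. The statements side by side.** Three sections (outcome criterion, Screening Investigations, Evaluation Outcomes) compare with baseline. Three (Methods Overview, Study Setting, Principal Findings) compare with L-thyroxine. Only the first set includes a sentence saying what result means efficacy. Statistical Analysis does not settle the matter.

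**3. Why TSH falls with no effect.** Assumed, not in the documents: log TSH = person level + independent within-person error, source median M = 2.0-2.5, between-person log SD σb = 0.5-0.6, within-person CV = 15-30%, and one qualifying value above 4.50 that also serves as baseline. Then:

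- σw² = ln(1 + CV²), s² = σb² + σw², ρ = σb²/s²
- z = [ln 4.50 − ln M]/s
- expected change in log TSH = −(1 − ρ) · s · φ(z)/[1 − Φ(z)]

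One setting by hand (M = 2.0, σb = 0.6, CV = 20%):

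- σw² = ln 1.04 = 0.0392; s² = 0.36 + 0.0392 = 0.3992; s = 0.632; ρ = 0.902
- z = ln(4.50/2.0)/0.632 = 0.811/0.632 = 1.28; φ(z)/[1 − Φ(z)] = 0.175/0.0997 = 1.76
- change = −0.098 × 0.632 × 1.76 = −0.109, a geometric mean ratio of exp(−0.109) = 0.90

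So TSH falls by about 10% on the geometric scale with no treatment effect.

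**4. Simulation over the whole grid, zero effect, n = 45 per arm.**

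| Quantity | Result |
|---|---|
| Geometric mean ratio, follow-up to baseline | 0.76-0.95 |
| Fall in arithmetic mean TSH | 4-19% |
| Participants falling by more than 20% | 21-55% |
| Trials with a significant fall, paired t test for any fall | 22-93% (nominal 2.5% in that direction) |
| Trials where the arm mean falls by more than 20%, CV 15-20% | under 1% |
| The same, CV 30% | 8-46% |
| Trials rejecting on a between-arm test of change | about 5% |

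The expected fall is present at every setting. Only its size varies. Two arms selected in the same way fall by the same expected amount, so the artefact cancels in the randomised comparison.

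**5. Sensitivity to a confirmed baseline.** If two values must exceed 4.50 and the second is the baseline, the same grid gives a fall of 2-12% and a significant paired fall in 9-56% of trials. T3 and T4 were not simulated; requiring both to stay in range could lower the participant-level proportions somewhat.

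**The case against.** The strongest reply is that the criterion only defines a change-from-baseline outcome, and that the comparison of arms is stated elsewhere. This has weight. A reader might infer that the trial will be analysed in the Ayurvedic arm alone. The documents do not support that: Methods Overview, Study Setting and Principal Findings state a comparison with L-thyroxine, and the t test is not said to be paired. What stands is that the only sentence saying what result means efficacy leaves the comparator out and conflicts with the design.

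A second reply concerns size. A reader might take 22-93% as the false-efficacy rate of the stated criterion. It is not: that figure tests for any fall, which matches the second sentence of the criterion read alone, whereas the first sentence asks for more than 20%. If the 20% applies to the arm mean, an inert regimen rarely passes at CV 15-20%. If it applies to each participant, 21-55% pass, but no required proportion of responders is given. So the risk depends on the reading.

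Third, the inputs are assumed. The eligibility list admits known cases, whose values may be stably high, and a repeat test before baseline would shrink the artefact. The article states no repeat test.

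Fourth, the contrast in the abstract is probably a slip, and the lifelong-treatment sentence is a conditional Discussion remark. Both still need correcting, but neither is evidence of regression to the mean. A reader might also infer that nothing is measured during the 180-day follow-up named under Course Duration. No measurement is tied to it in the text, but the SPIRIT schedule figure is not available here, so this cannot be asserted of the plan.

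**Conclusion.** The point holds in this form: the efficacy conclusion is tied to a fall from baseline in one arm, it contradicts the declared randomised superiority comparison, and it should be corrected. The contradiction, and the possibility of calling the regimen efficacious when it does worse than L-thyroxine, need no assumption. The direction of the regression artefact follows from selecting on TSH above 4.50 wherever TSH varies within persons. Its size rests on the assumed TSH distribution and on a single qualifying value used as baseline, and ranges from small to large according to how the 20% threshold is read. The documents do not show that a between-arm analysis will be omitted, and a separate analysis plan could supply its details. That would not repair a published criterion that fixes the conclusion on the wrong contrast.

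**What to change.** - **Outcome criterion.** Replace the sentence that equates a fall in TSH with efficacy. State that efficacy rests on the between-arm difference in day-181 TSH, Group A versus Group B, adjusted for baseline TSH (on the log scale if skewed), with its confidence interval.
- **Screening Investigations and Evaluation Outcomes.** Report within-arm change descriptively. Keep the 20% criterion as a description, or as a responder proportion compared between arms, and stop calling it statistical significance.
- **Abstract, Results.** Name the contrast as the Ayurvedic regimen versus L-thyroxine.
- **Principal Findings.** Remove the statement about eliminating lifelong L-thyroxine, which a day-181 outcome cannot support.
- **Course Duration.** Reconcile the stated 180-day follow-up with the stated day-181 outcome timing.

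These are changes of wording, with no new visit or test. The price is that the efficacy conclusion becomes harder to reach, because the regimen must then be shown to do better than L-thyroxine rather than better than its own baseline.

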### Interventions for the Study Group

#### Deepan-Pachan

Shivakshar Pachak Churna is an Ayurvedic medication that should be taken orally, with a dosage of 1 gram, twice a day, for 3 days (Table 1). Before commencing Basti therapy, it will enhance the appetite, a crucial factor. The preparation will be conducted in the pharmacy that is connected to our institute.

**Table 1 table1:** Contents of Shivakshar Pachak Churna.

Ayurvedic name	Latin name/English name
Sunthi	*Zingiber officinale*
Marich	*Piper nigrum*
Pippali	*Piper longum*
Ajmoda	*Trachyspermun roxburghianum*
Jeeraka	*Cuminum cyminum*
Krishnajeerak	*Nigella sativa*
Hingu	*Ferula asafoetida*
Haritaki	*Terminalia chebula*
Saindhav	Rock salt
Sajjikshar	Carbonate of soda

#### Kanchanar Guggul [10]

It will be prepared in the pharmacy attached to our hospital. It will be designed per the standard operating procedure (SOP) mentioned in the pharmacy attached to the hospital. The contents are provided in the table (Table 2).

**Table 2 table2:** Contents of Kanchnar Guggul.

Ayurvedic name	Latin name
Kanchanar	*Bauhinia variegata linn*
Amalaki	*Embelica officinalis*
Haritaki	*Terminalia chebula*
Bhibtak	*Terminalia bellirica*
Pippali	*Piper longum*
Varuna	*Crateva religiosa*
Dalchini	*Cinnamomum cassia*
Ela	*Elettaria cardamomum*
Tejpatra	*Cinnamomum tamala*
Guggul	*Commiphora wightii*

#### Kshar Basti and Its Procedure

##### Preoperative

Kshar Basti [12] is a therapeutic decoction enema [14]. Therefore, we will follow the same operative procedures that apply to Niruha Basti. The Yoga Basti method (Figure 3) will administer Niruh Basti and Anuvasan Basti (therapeutic unctuous enemas) on alternate days, except the last day. For 3 days, we will administer Deepan-Pachan, which enhances metabolic fire. Kshar Basti’s decoction will be prepared per the SOPs followed in the hospital. Table 3 lists Kshar Basti's contents. For the Anuvasan Basti, we will use plain sesame oil. We will call the participants to the hospital early for the Kshar Basti during the day (before 3 PM). Sesame oil massage and hot fomentation will be performed on the whole body. The fomentation will be conducted as per the SOPs of the hospital as mentioned by the National Accreditation Board for Hospitals.

**Figure 3 figure3:**
[figure not shown]
Intervention details. KB: Kshar Basti; OE: oil enema; SCH: subclinical hypothyroidism.

**Table 3 table3:** Contents of Kshar Basti.

Content	Quantity
Jaggery (Guda)	100 g
Tamarind pulp (Amlika)	100 g
Rock salt (Saindhav)	10 g
Cow’s urine (Gomutra)	400 mL
Paste of Anthem Sova (Shatavha Kalka)	10 g
Total	500 mL

##### Operative

The raw medicines will be collected, prepared, and made lukewarm by indirect heating. Materials will be taken into an enema can. The participant will be asked to lie over the table in the left lateral position. The nozzle of the enema can be slowly inserted into the anal canal after applying oil to it. It will be slowly inserted till it reaches the rectum, and now the decoctions will enter the rectum. Soon after the administration of Kshar Basti, the participant will be allowed to defecate.

##### Postoperative Period

The participant will be asked to follow a dietary regimen like Yusha (a soup of vegetables or pulses) and rice and drink hot water during the Kshar Basti course.

##### Course Duration

Basti will be administered daily for 8 days; after that, the participant must follow the regimen for 16 days. The total duration of the course will be 27 days (including Deepan-Pachan for 3 days), and after this course, Kanchanar Guggul will be administered for 153 days. The duration of the therapy will be 180 days, and the follow-up period will be 180 days.

Both groups of patients are restricted from taking or consuming any medications, devices, or nonpharmacological treatments that have an impact on hypothyroidism.

### Sample Size Calculations

We used the following formula for the determination of sample size (N=40) [15]:

Thus, there will be 45 participants in each group (5 added to minimize the error), and our study’s sample size will be 90 (n=90).

We also noted the sample size utilized in past studies conducted on hypothyroidism at this institute. Thus, a sample size of 90 would be both practical and adequate.

(N=size per group; *z*_1–_*_α_*= the standard normal deviate for one group; *z*_1–_*_β_*= the standard normal deviate for the other group, δ_0_= a clinically acceptable margin.)

### Data Collection Methods

The researcher will gather and archive the data. The data will be collected using appropriate software, such as Epi-Info. We will examine the data after the trial concludes. Replicates will be discarded. We will choose a conventional laboratory to quantify serum TSH.

### Data Confidentiality

Only the PhD guide will have access to the acquired data, which includes biological samples from the individuals. However, upon completion of the study, any researcher may request access to the data for a systematic review and meta-analysis.

### Audit

We will conduct the audit 6 months after the trial begins, under the supervision of a PhD mentor. Furthermore, we will closely observe and track any negative reactions caused by the drugs or treatments used in our operations, as well as ensure strict adherence to the established protocol.

We will educate the participants about the favorable attributes of Kshar Basti (the therapeutic enema), to ensure their compliance with the treatment regimen and adherence to the established procedures. We will closely observe the reduction in participants from this experiment and the factors contributing to this reduction.

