#### Secondary Objective

Our secondary goal is to evaluate the appropriateness of Basti Karma (rectal enema therapy) and determine the dropout rate of the Basti course.

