**Withdrawal criteria:**
The participant may be withdrawn from the trial if there is one of the following:Any adverse event and adverse drug reaction (ADR) occurrenceVoluntary withdrawal by the participantViolation of inclusion and exclusion criteriaThere is noncompliance with the treatment regimen (a minimum of 80% compliance is essential to continue in the study)

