**Criteria for discontinuing from the trial**
If the participant breaks the sequence of panchakarma therapy and misses the oral therapy for ≥7 days, he/she will not be considered in the trial.

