## Results

### Overview

We will examine the following factors in the demographics: age, gender, location, smoking behavior, alcohol consumption, and the type of salt used to achieve the secondary purpose of this study. We will examine the rate at which participants drop out of the Kshar Basti course, as well as any occurrences of difficulties associated with the Kshar Basti course.

We will only recruit participants for this study once. We will finish the drug preparation and acquisition by June 2024. The projected timeline for the recruitment process is June 2024 to December 2025. We will evaluate the information right away and conclude at the start of 2026.

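### Education on the merits of Kshar Basti, given to secure compliance, acts on the Basti dropout rate that the secondary objective sets out to estimate

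*Protocol article*

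**What the plan says.** The Audit section plans participant education in these terms: "We will educate the participants about the favorable attributes of Kshar Basti". The same sentence gives compliance with the regimen as the purpose. The same section says the trial will "closely observe and track any negative reactions caused by the drugs or treatments used in our operations", and also: "We will closely observe the reduction in participants from this experiment and the factors contributing to this reduction".

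The Secondary Objective is to evaluate how appropriate Basti therapy is and to "determine the dropout rate of the Basti course". The Overview under Results repeats this: "We will examine the rate at which participants drop out of the Kshar Basti course", together with difficulties arising from the course.

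Two rules in the eligibility textbox tie staying in the trial to compliance. The withdrawal criteria add to non-compliance the note that "a minimum of 80% compliance is essential to continue in the study". Under the discontinuation criteria, a participant who breaks the panchakarma sequence and misses oral therapy for 7 days or more falls under the words "he/she will not be considered in the trial".

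Study Setting calls the trial single-blind, and Blinding says it is the researcher who is blinded. No blinding of participants is described.

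**The concern.** A dropout rate is behavioural. Unlike a serum TSH value, it responds directly to what participants are told and how they are encouraged. Teaching the merits of the enema course so that people complete it, and then reporting how many completed it as evidence on whether the course is appropriate, mixes the acceptability of the treatment with the effect of the persuasion.

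What is at stake is mainly the secondary result. A low dropout rate would be read as showing that patients tolerate the course, when part of it may be due to promotion that would not accompany routine use.

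There is a second, weaker route. Participants can tell an enema course from a daily tablet, and the compliance rules govern who remains in follow-up. Encouragement tied to one treatment could therefore change who is still present in each arm for the day-181 measurements.

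**Working it through.** The point rests on how the sections fit together. The document gives no expected dropout rate for either arm and no figure for the effect of the education, so there is no plan figure to reproduce.

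**Step 1: the sections side by side.**
- Audit fixes the content of the education (merits of the enema), its direction (favourable) and its purpose (compliance). This is a stated choice, not a gap.
- Secondary Objective and Results, Overview, make dropout from that course a quantity to be estimated.
- The intervention and the estimated quantity are therefore the same behaviour seen from two sides.

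**Step 2: direction.** Let d0 be the dropout rate without the education and e the reduction that it brings. The observed rate is d0 − e. If the education does what it is meant to do, e is above zero and the observed rate understates d0. If it does nothing, e is zero. An upward shift would need the education to backfire. Probably downward is therefore a fair reading. The size of e is unknown.

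**Step 3: what a shift would look like (assumed counts).** The Grouping section gives 45 participants per arm, so one participant is 1/45 = 2.2 percentage points. Starting from an assumed 9 dropouts, with exact (Clopper-Pearson) 95% intervals:

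| Dropouts | Rate | 95% interval |
|---|---|---|
| 9/45 | 20.0% | 9.6% to 34.6% |
| 7/45 (two fewer) | 15.6% | 6.5% to 29.5% |
| 5/45 (four fewer) | 11.1% | 3.7% to 24.1% |
| 4/45 (five fewer) | 8.9% | 2.5% to 21.2% |

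Five fewer dropouts would lower the rate by 5/45 = 11.1 points, to 4/9 = 44% of its starting value. The intervals overlap widely, so sampling error at this size is as large as the shift. But the interval describes chance only. It neither covers nor reveals a systematic shift.

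**Step 4: would unequal retention be noticed?** Power to detect a difference in dropout between arms, with 45 per arm, two-sided 0.05, normal approximation with pooled variance under the null, on assumed rates:
- 20% versus 30%: 19%
- 10% versus 20%: 26%
- 5% versus 20%: 58%
- 10% versus 30%: 66%

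For 10% versus 20%: the critical difference is 1.96 × √(2 × 0.15 × 0.85 / 45) = 0.148; the standard error under the alternative is √((0.09 + 0.16) / 45) = 0.0745; (0.10 − 0.148) / 0.0745 ≈ −0.64, which gives power of about 26%. A moderate difference would often not reach significance. This shows limited ability to detect a difference, not that one will arise.

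**The case against.** The strongest reply has five parts.

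- **The information is not shown to be one-sided overall.** A reader might infer that participants hear nothing but praise for the enema. The text does not say so. Ethical Considerations has participants informed about procedures and medications before written consent, with further consent for panchakarma later, and Audit commits to tracking negative reactions. This stands. It does not remove the effect of later encouragement whose stated purpose is compliance.
- **Dropout under encouragement is a legitimate descriptive result.** This stands if the encouragement is described alongside the rate. It would be too strong to say that the rate tells nothing about acceptability.
- **Counselling in the levothyroxine arm may be in the full protocol.** A condensed article can leave that out, and its absence here is no fault. The point rests on what Audit states about Kshar Basti.
- **The effect on retention has no known direction.** A course with repeated hospital attendance may lose more people than a daily tablet, so support for it could narrow a gap as easily as widen it. A reader might also infer that controls would leave on hearing the enema praised. Nothing says that controls receive this education, and the mention of the treatment regimen suggests it is meant for those on Kshar Basti.
- **Removal for non-compliance is a separate matter.** The withdrawal and discontinuation rules change who is followed whether or not anyone is coached, and a neutral script would leave them in place. TSH is also a laboratory value, so expectation does not colour its measurement. Both statements stand. The education can reach the primary comparison only through adherence and retention.

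**Conclusion.** The concern holds for the secondary objective. Carried out as written, the Audit sentence acts on the dropout rate that the trial sets out to determine, and probably makes it lower than it would be without promotion. This rests on one assumption: that the education has some of its intended effect. The size cannot be derived from the document, and the counts above only illustrate what a few participants mean in an arm of 45.

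Different retention by arm is a possibility and no more. A reader might infer that the plan makes retention differ in what is in effect an open-label trial. The document's own label is single-blind, with the researcher blinded. What can be said is that no participant blinding is described and that the arm is evident from the treatment. A bias figure for TSH would need a difference in loss between arms and a TSH gap between those lost and those retained. The document gives neither, so none is claimed.

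This is worth considering as a cheap improvement to a secondary, descriptive outcome. It is no threat to the trial's main result on the evidence shown.

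**What to change.** Replace the sentence in Audit with wording such as: participants in both arms receive the same neutral, scripted adherence instruction about their own allocated treatment, at equivalent contacts, with no statement about the expected benefit of either treatment.

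Add to the Secondary Objective or Results, Overview: dropout from the Basti course is reported with reasons, and the denominator is all participants randomised to Kshar Basti, including anyone withdrawn for non-compliance or discontinued. It is best to define this group by treatment, because the opening sentence of Interventions and the textbox beneath it assign the treatments to Groups A and B in opposite ways.

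The cost is one script and two sentences. Completion of the enema course may be slightly lower, but that is the behaviour the secondary objective is there to measure. No dose, schedule or clinical rule is affected.
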